## Abstract

**Background:**

Treatment options for patients with advanced hepatocellular carcinoma (HCC) are often limited. In most cases, they are not amenable to local therapies including surgery or radiofrequency ablation. The multi-kinase inhibitor sorafenib has shown to increase overall survival in this patient group for about 3 months.

Radiation therapy is a treatment alternative, however, high local doses are required for long-term local control. However, due to the relatively low radiation tolerance of liver normal tissue, even using stereotactic techniques, delivery of sufficient doses for successful local tumor control has not be achieved to date.

Carbon ions offer physical and biological characteristics. Due to their inverted dose profile and the high local dose deposition within the Bragg peak precise dose application and sparing of normal tissue is possible. Moreover, in comparison to photons, carbon ions offer an increased relative biological effectiveness (RBE), which can be calculated between 2 and 3 depending on the HCC cell line as well as the endpoint analyzed.

Japanese Data on the evaluation of carbon ion radiation therapy showed promising results for patients with HCC.

**Methods/Design:**

In the current Phase I-PROMETHEUS-01-Study, carbon ion radiotherapy will be evaluated for patients with advanced HCC. The study will be performed as a dose-escalation study evaluating the optimal carbon ion dose with respect to toxicity and tumor control.

Primary endpoint is toxicity, secondary endpoint is progression-free survival and response.

**Discussion:**

The Prometheus-01 trial ist the first trial evaluating carbon ion radiotherapy delivered by intensity-modulated rasterscanning for the treatment of HCC. Within this Phase I dose escalation study, the optimal dose of carbon ion radiotherapy will be determined.

**Trial registration:**

NCT 01167374

## Background

Primary liver cancer is the fifth most common neoplasm in the world, and the third most common cause of cancer-related death; of those, hepatocellular carcinoma (HCC) amounts to about 75-90% [1]. More than 600 000 new cases are diagnosed yearly, with and incidence of 5.5 to 14.9 per 100 000 [2,3]. In some areas of Asia, HCC is endemic, and is the most common cause of death due to cancer [4,5]. In Europe and the USA, HCC has shown an increase in incidence over the last years, which is attributed to an increase in Hepatitis C-Virus (HCV) infections [6-10]; other main risk factors include cirrhosis, alcohol or haemochromatosis [11].

It is known, that in Europe, North America and Japan, HCV-related HCC represents about 75% of all cases, where as in the Asia-Pacific Region (excluding Japan) 70% of all patients with HCC are diagnosed with chronic Hepatitis-B-Virus (HBV)-infections [12].

In Western countries, about 30-40% of all patients with HCC are diagnosed with early stages of the disease and potentially curative treatments such as surgical resection, liver transplantation (TPX) or locoregional procedures such as radiofrequency ablation of chemoembolisation can be performed, depending on liver function and tumor burden. In well selected patient groups, overall survival (OS) rates of 60 - 70% at 5 years have been observed [13].

However, treatment options for patients with advanced staged HCC are limited and this patient group is associated with a poor prognosis [13]. In the past, no systemic chemotherapeutic treatment regimen has improved outcome in patients with advanced HCC [14-16]. New substances addressing single molecular targets, such as EGFR-inhibition with cetuximab, have not demonstrated convincing results [17]. Only recently, however, the multi-kinase inhibitor sorafenib (Nexavar^®^) has been shown to be effective in patients with HCC: In the multicenter SHARP trial (Sorafenib Hepatocellular Carcinoma Assessment Randomized Protocol), an increase in OS in patients with advanced HCC from a median of 7.9 months in the placebo group to 10.7 months in the sorafenib group could be demonstrated [18]. The study included 602 patients in a double-blind setting, and treatment with sorafenib was performed with 400 mg bid or placebo. Although OS and time to radiological progression were increased significantly, time to symptomatic progression (determined by the Functional Assessment of Cancer Therapy-Hepatobiliary Syndrom Index 8 (FHSI8) questionnaire or the occurrence of unacceptable adverse events or death) was not changed. Moreover, according to the RECIST-criteria, most controlled patients only showed stable disease in imaging, and only 2 out of 229 patients treated with sorafenib showed a partial response of the HCC; no complete remissions were observed.

Another randomized phase III trial evaluating efficacy and safety of sorafenib in patients with advanced HCC was performed in the Asia-Pacific region, and also demonstrated good tolerability of sorafenib and an increase in OS from 4.2 months to 6.5 months [19]. Again, time to symptomatic progression was unaltered by sorafenib, and the vast majority of patients controlled with sorafenib showed stable disease, with only 5 out of 150 partial responses and no complete remissions.

Therefore, this group of patients with advanced HCC is still characterized by unsatisfactory outcome, and treatment optimization is needed.

External Beam Radiotherapy has been applied for the treatment of HCC in the past with only moderately convincing clinical results. With conventional photon techniques, dose tolerance of surrounding normal liver tissue has been a major problem and has limited application of high local doses to larger liver tumors. Radiation induced liver disease (RILD), which is defined as a veno-occlusive disease leading to development of ascites, icterus, increase in liver enzymes and hepato-encephalopathy, is known to develop with total doses of 30-35 Gy delivered to the total liver [20]. However, more conformal radiation techniques have been shown to be safe, however only moderately effective, in patients with HCC, mainly due to the known dose-response-relationship of liver tumors [20-22]. Park et al. could show that patients treated with total doses of > 50 Gy showed significantly higher outcome and increased rates of partial tumor responses after radiotherapy in 158 patients with HCC treated with 3D-conformal radiotherapy with increasing doses [23]. Among other studies, this group could show that dose was the only reproducible prognostic factor for tumor control [23,24]. However, as total doses are increased even using 3D-conformal photon techniques, the rates of radiation-induced side effects increase, and therefore application of higher and locally effective radiation doses are limited especially in larger tumors.

Using stereotactic photon treatments, functional normal liver tissue may be spared more effectively. In the past, several groups have implemented extracranial stereotactic treatment for liver tumors in single-dose or hypofractionated settings, however, with increasing tumor sizes which is common in HCC, dose application is again limited [25-28].

Therefore, treatment of patients with advanced stage HCC is often limited to systemic treatment with sorafenib.

However, new radiation modalities such as particle therapy offer distinct physical and biological characteristics and are a promising treatment alternative for patients with HCC.

Heavy charged particles provide the physical advantage of an inverted dose profile which enables steep dose gradients. Neighboring organs at risk and surrounding normal tissue can be spared from radiation doses. Additionally, carbon ions, as high-LET beams, are characterized by an enhanced relative biological effectiveness (RBE). For hepatocellular carcinoma cell lines, RBE values between 2 and 3 have been reported depending on cell line and endpoint [29,30]. In general, high local doses are required for long-term local tumor control in patients with HCC. The distinct physical dose characteristics of particle therapy allow the application of higher local doses while sparing healthy normal tissue, which was a limiting factor in the application of radiation doses for the treatments of HCC with conventional radiation techniques. Results of proton radiotherapy in patients with HCC reported from Japan are promising, even in patients with advanced tumors [31-37]. Carbon ions offer, additionally to the same physical benefits, an increase relative biological effectiveness, which has been shown to be beneficial with respect to outcome in several different tumor entities [38]. Results from carbon ion radiotherapy for the treatment of patients with HCC have shown safety and high local control and response rates [38-40].

In Chiba and Tsukuba, researchers have evaluated ion beam radiotherapy in patients with HCC showing promising results. Kawashima and colleagues treated 30 patients with solitary HCC not amenable to surgery or local ablation therapy with protons with total doses of 76 Gy E in single fractions of 3.8 Gy E [33]. All patients had liver cirrhoses, which was Child A in 20 and Child B in 10 patients. No severe side effects were observed, and 2-year actuarial local progression-free rate was 96%, with an actuarial OS rate of 66%. Out of 30 patients, 24 developed a complete response of the HCC. The Tsukuba group demonstrated local control of 93% after 5 years in patients with HCC with limited treatment options other than radiotherapy [35]. In this study, total doses of 63-84 Gy E proton radiotherapy were applied in a fractionated regimen using 13 to 27 fractions. OS rates were 62% and 33% at 2 and 5 years. No toxicities ≥ Grade III were observed, and treatment was well tolerated. The same group could also demonstrate that high-dose proton radiotherapy may be applied safely in patients with HCC associated with a portal vein tumor thrombus, severe liver cirrhosis or even in the aged patient population [31,34,37].

Carbon ions additionally offer a higher biological effectiveness due to the characteristic and severe radiation damages produces in target tissues. Is has been shown that carbon ion radiotherapy leads to an increased in local control especially in radiation resistant tumors, such as chordomas and chondrosarcomas, adenoidcystic carcinomas, melanomas as well as HCC [38]. Kato an colleagues treated 24 patients with HCC with carbon ion radiotherapy in a dose-escalation study increasing total doses from 49.5 Gy E to 79.5 Gy E in dose increments of 10% in a fixed 15 fraction setting [39,40]. It could be shown that dose increase was safe without severe treatment associated side effects, even in the highest dose groups. The optimal dose was determined to be 72 Gy E, which was the lowest dose to show the highest local tumor control without grade III toxicity. In this group, the overall tumor response rated was 71%, with a complete response in 10 out of 24 patients, and a partial response on 7 out of 24 patients.

Although patient collectives in these studies on particle therapy and on the treatment of patients with sorafenib are heterogeneneous, the data show that particle therapy may be a successful treatment alternative for patients with advanced HCC.

In the present PROMETHEUS-01 trial, carbon ion radiotherapy will be evaluated in patients with advanced HCC.

Since 1997, carbon ion radiation therapy is available by the Department of Radiation Oncology, University Hospital of Heidelberg, at the Gesellschaft für Schwerionenforschung in Darmstadt, Germany. Clinical studies on skull base tumors, brain tumors as well as head-and-neck-tumors with skull base invasion treatment safety could be demonstrated. Based on the clinical results, the Heidelberg Ion Therapy Center (HIT) was built delivering ion beams with equivalent technology. Worldwide, particle therapy is available in the clinical routine in a large number of centers.

At the University of Heidelberg, patients with HCC are treated in the interdisciplinary setting consisting of visceral surgery, internal medicine/gastroenterology, radiology and radiation oncology. Therefore, patients will be provided the best possible oncological care on a professional basis.

## Methods/Design

### Study design

The trial will be performed as a single-center Phase I Dose Finding study.

Patients fulfilling the inclusion criteria will be included into the following Phase I dose escalation treatment scheme shown in Table 1.

**Table 1 T1:** Treatment scheme for dose escalation.

Step 1:	4 × 10 Gy E	40 Gy E
Step 2:	4 × 11 Gy E	44 Gy E

Step 3:	4 × 12Gy E	48 Gy E

Step 4:	4 × 13 Gy E	52 Gy E

Step 5:	4 × 14 Gy E	56 Gy E

### Trial Design

The study is performed as a one-armed single center Phase I trial. The treatment schedule is shown in the study flow chart in Figure 1.

**Figure 1 F1:**
[figure not shown]
**Flow chart of the Prometheus-01 study**.

### Study objectives

The purpose of the trial is to evaluate carbon ion radiotherapy in patients with advanced HCC. With respect to toxicity, the optimal dose of carbon ion radiotherapy will be determined. Therefore, the primary endpoint is toxicity, secondary endpoints are evaluation of progression-free survival, response, and overall survival after carbon ion radiotherapy.

Focus of the analysis is to evaluate safety and efficacy of carbon ion radiotherapy in patients with HCC. Therefore, the aim of the trial is to observe low rates of toxicity with high local doses due to effect of the altered biology of carbon ions on HCC as well as the superior physical characteristics.

#### Primary Objective

The primary objective is toxicity of carbon ion radiotherapy and the definition of a MTD for subsequent clinical investigation of carbon ion radiotherapy.

#### Secondary Objectives

The secondary objectives of the study are imaging response and progression-free survival.

### Patient selection: Inclusion criteria

Patients meeting all of the following criteria will be considered for admission to the trial:

- histologically confirmed HCC or diagnosis of HCC according to AASLD-guidelines

- macroscopic tumor

- liver-confined disease without extrahepatic disease as diagnosed by CT, MRT, ultrasound and bone scan

- minimal distance of tumor edge to the intestines of 1 cm

- age ≥ 18 years of age

- Karnofsky Performance Score ≥60

- For women with childbearing potential, (and men) adequate contraception.

- Ability of subject to understand character and individual consequences of the clinical trial

- Written informed consent (must be available before enrolment in the trial)

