### Patient selection: Exclusion criteria

Patients presenting with any of the following criteria will not be included in the trial:

- refusal of the patients to take part in the study

- previous radiotherapy of the hepatobiliary system

- margin of < 1 cm between tumor edge and intestines

- Patients who have not yet recovered from acute toxicities of prior therapies

- Known carcinoma < 2 years ago (excluding Carcinoma in situ of the cervix, basal cell carcinoma, squamous cell carcinoma of the skin) requiring immediate treatment interfering with study therapy

- Pregnant or lactating women

- Participation in another clinical study or observation period of competing trials, respectively

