### Trial Duration, Schedule and Follow-up

The primary endpoint is acute toxicity of carbon ion radiotherapy observed within 30 days of study treatment.

Patients are scheduled for follow-up visits every 4 weeks after completion of carbon ion radiotherapy for the first 3 months, thereafter in 2-months intervals or as needed clinically including contrast-enhanced MRI as well as thorough clinical-neurological and haematological assessment. These follow-up visits are in line with standard care outside of clinical trials.

The last patient included into the study will be followed for at least 3 months after study treatment. This is considered the final study visit. All other patients will be followed regularly as described in detail until death or until 3 months after LPI.

The overall duration of the trial is expected to be approximately 24 months.

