### Statistical calculations for trial sample size

#### Study hypothesis

The study is designed to demonstrate that carbon ion radiotherapy is safe for the treatment of HCC. The aim of the study is to evaluate the optimal dose tolerated with respect to toxicity.

Unacceptable toxicity (DLT) is defined as any irreversible grade 4 toxicity during a time frame of 30 days as classified by CTCAE version 4.0.

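### Eligibility sets no minimum hepatic reserve, so decompensation from underlying cirrhosis can be scored as a DLT and pull down the MTD

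*Protocol article*

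**What the plan says.** **Eligibility.** The inclusion section opens with "Patients meeting all of the following criteria will be considered for admission to the trial" and lists nine criteria. The only one that measures fitness is "Karnofsky Performance Score ≥60". The exclusion section lists seven items, and the only one specific to the liver is "previous radiotherapy of the hepatobiliary system", apart from the tumour-to-bowel margin. Neither list mentions Child-Pugh class, bilirubin, ascites, encephalopathy or any other measure of hepatic reserve.

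**The limiting tissue.** The Background says of conventional photon techniques that "dose tolerance of surrounding normal liver tissue has been a major problem and has limited application of high local doses", and the Abstract makes the same point about liver tolerance. The Background describes radiation-induced liver disease (RILD) as "defined as a veno-occlusive disease leading to development of ascites, icterus, increase in liver enzymes and hepato-encephalopathy". It also names cirrhosis among the main risk factors for HCC. For one proton series it reports hepatic reserve explicitly: "All patients had liver cirrhoses, which was Child A in 20 and Child B in 10 patients".

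**DLT and escalation.** Study hypothesis states: "Unacceptable toxicity (DLT) is defined as any irreversible grade 4 toxicity during a time frame of 30 days". Three further definitions follow under Sample Size Calculation, Analysis Variables and Descriptive Analysis. Escalation is a 3+3 scheme over five steps. It continues after no DLT in three patients or exactly one in six; two or more in six stop it, and the next lower step becomes the MTD.

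**The concern.** The signs the article gives for RILD (ascites, jaundice, raised enzymes, encephalopathy) are also those of cirrhosis that is decompensating on its own. With no entry limit on hepatic reserve, nothing in the plan bounds how often such events arise from the underlying disease within the 30-day window. The trial has one arm, so there is no comparison group to show how many would have occurred anyway.

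The primary endpoint is exposed because each dose step is judged on three to six patients and two scored events end the escalation. The MTD could then reflect who was enrolled and not the dose. A separate safety concern does not depend on any rate: the patients with the least reserve against liver injury can enter a dose-escalation study of liver irradiation.

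**Working it through.** **1. The plan's own figure.** Sample Size Calculation gives a maximum of 33: four steps of up to 6 patients plus 9 at the MTD. 4 × 6 + 9 = 33, which reproduces.

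**2. Can background decompensation be scored as a DLT?** The four definitions side by side:

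| Section | Grade 4 must be irreversible? | Relation to treatment required? |
|---|---|---|
| Study hypothesis | Yes | No |
| Sample Size Calculation | Yes | No |
| Analysis Variables | Irreversible or, on the apparent reading, unpredictable | Yes; possible is enough |
| Descriptive Analysis | No | Yes; possible is enough |

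Each version leaves a route. Under the first two, irreversible progression of cirrhosis counts whatever its cause. Under the last two, decompensation within 30 days of liver irradiation would have to be judged not even possibly related to escape scoring, which is hard to do in a single-arm trial.

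**3. Effect on escalation.** Let p be the probability per patient of a *scored* DLT arising from background liver disease alone, after whatever attribution and irreversibility filter is applied. The documents do not give p; it is assumed over a range. From the stated rule:

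P(escalate at one step) = (1 − p)^3 + 3p(1 − p)^2 × (1 − p)^3 = (1 − p)^3 + 3p(1 − p)^5

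Two or three DLTs in the first three patients also lead to a second cohort as the rule is worded, but the step cannot then be cleared, so the formula is unaffected.

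P(stop before step 5 is cleared) = 1 − P(escalate)^5, with no dose-related toxicity at any step.

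For p = 5%: 0.95^3 = 0.8574; 3 × 0.05 × 0.95^5 = 0.1161; the sum is 0.9734; 0.9734^5 = 0.874; 1 − 0.874 = 12.6%.

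| Assumed p | Escalate at one step | Stop before step 5 is cleared | Stop at step 1 |
|---|---|---|---|
| 0 | 1.0000 | 0% | 0% |
| 2% | 0.9954 | 2.3% | 0.5% |
| 5% | 0.9734 | 12.6% | 2.7% |
| 10% | 0.9061 | 38.9% | 9.4% |
| 15% | 0.8138 | 64.3% | 18.6% |

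A stop at step 1 leaves no lower step in Table 1 to name as the MTD.

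**4. With some true toxicity.** Assume treatment-related DLT risks d of 2, 4, 8, 15 and 25% at steps 1 to 5 (illustrative), a background rate b, and a combined risk of 1 − (1 − b)(1 − d).

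| Background b | Stop at step 3 or lower | Clear all five steps |
|---|---|---|
| 0 | 8.4% | 44.7% |
| 5% | 24.2% | 28.6% |
| 10% | 43.4% | 15.9% |

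The shift is towards a lower MTD in every case.

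**The case against.** **DLT filters.** Two definitions demand relatedness and two demand irreversibility, so many background events would not count. This stands as a limit on size: p is the rate after filtering. If 10% of patients decompensated and half of those events were scored, p would be 5% and the stopping probability 12.6%, not 38.9%. It does not remove the problem, because no definition closes the route. Part of the confounding does come from the inconsistent definitions and not from eligibility alone, so the fix must cover both.

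**Compulsory enrolment.** A reader might infer that any decompensated patient with Karnofsky 60 has to be admitted. The text says only that eligible patients are considered for admission. The article also describes interdisciplinary care that includes gastroenterology, and requires that patients can understand the trial, which bears on overt encephalopathy. None of this is a hepatic-reserve limit, but the supportable statement is that such a patient may be enrolled.

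**Liver failure as the named limiting toxicity.** The protocol does not say this. It discusses RILD and liver tolerance in the background on photon treatment; its own DLT is any qualifying grade 4 toxicity.

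**Grade 4 at baseline.** A pre-existing value is not automatically a DLT, because the definitions place the event in a window or after treatment. The difficulty is that such a patient cannot be assessed cleanly for that parameter.

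**Visit assessments.** Follow-up lists "thorough clinical-neurological and haematological assessment" without naming liver chemistry. One might infer that liver function goes unmeasured. The article does not support that: a laboratory panel is detail that an article leaves to the full protocol.

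**Survival in the sorafenib trials.** The control-arm medians quoted in the Background might be read as a guide to p. They reflect deaths from any cause in a different setting and say nothing about scored hepatic events, so they are not used here.

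**Deliberately open entry.** The Background reports proton treatment given safely in severe cirrhosis. That is a fair defence of breadth, but it concerns protons, and the carbon ion series described there used 15 fractions against 4 in Table 1. The article does not offer it as the reason for having no criterion, and breadth would still leave the scoring problem.

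**Conclusion.** The point holds. Both eligibility lists are printed in full, down to contraception and refusal to take part, so the absence of a hepatic-reserve criterion cannot be put down to condensation. Taken with DLT definitions that either need no attribution or accept a possible one, the plan as written allows underlying cirrhosis to stop the escalation and lower the MTD.

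The size is conditional. The chance of a stop caused by background events alone is negligible at p = 2% (2.3%), material at 5% (12.6%) and serious at 10% to 15% (38.9% to 64.3%). These figures assume independent patients, a constant p across steps and no dose toxicity. The documents neither give p nor contain an entry limit that would keep it low. They do not show that a wrong MTD is likely; they show that the design does not protect against one. Nor do they support a particular Child-Pugh cut: the Child A and B mix comes from one 30-patient proton series, and no Child class is stated for the cited carbon ion series.

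**What to change.** 1. Add a baseline hepatic-reserve criterion to the inclusion list. The investigators should choose and justify the measure and threshold; none is proposed here.
2. Exclude patients who already have grade 4 values in parameters that count towards DLT.
3. Record liver function at baseline and score a hepatic DLT as a change from that baseline.
4. Reconcile the four DLT definitions so that one text, used everywhere, settles attribution and irreversibility, including how decompensation from the underlying disease is to be attributed.

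The cost is an amendment to the two eligibility lists and the DLT text, and the loss of a few decompensated patients from recruitment. The escalation rule and the maximum of 33 patients do not change.
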